### Withdrawal criteria

Participants will be withdrawn from the study if any of the following occur:

(1) Participants who develop intolerable severe withdrawal symptoms during the NBZDs tapering process.(2) Voluntary withdrawal at the participant’s request.(3) Withdrawal of informed consent.(4) Emergence of exclusion criteria during the study period.(5) Poor treatment compliance, defined as attendance at fewer than 50% of scheduled acupuncture sessions.(6) Occurrence of adverse events that preclude continued participation or pose a risk to participant safety.

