### Outcome measures

#### Primary outcome measures

The successful discontinuation rate at the end of the 6-week treatment was defined as the proportion of patients who had completely ceased NBZDs use (any dose) during the final week of treatment (days 36–42). Medication adherence was verified using patients’ daily diaries and medication records. Patients completed a daily diary card, on which they recorded the date, medication name, dose, time of administration, and any adverse reactions. The diary cards were returned to the physician at each weekly visit, and prescription records were cross-checked by an independent observer every 3 weeks. Any discrepancy between the diary and medication records will be resolved by consensus of two blinded independent investigators based on all available data (daily diaries, medication records). Urine or blood drug concentration testing was not performed to confirm participants’ self-report of hypnotic discontinuation, due to the short half-life of NBZDs (requiring daily sampling, which is logistically infeasible) and the increased participant burden that would likely raise dropout rates. The multi-source adjudication approach described above was considered a reliable alternative.

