Objective sleep measures (PSG and ACT) were not collected at the 10-week follow-up because the primary focus of this trial was NBZDs discontinuation, not direct sleep improvement. To enhance patient convenience and retention, some participants will be followed up online (video/phone) at week 10, precluding in-person objective measurements. PSG is resource-intensive and burdensome, and actigraphy requires prolonged device wear, both of which could increase dropout rates in this pragmatic feasibility study.

(5) *Assessment of acupuncture treatment expectancy*

The Acupuncture Expectancy Scale (AES) is a four-item instrument rated on a 5-point Likert scale, yielding total scores ranging from 4 to 20 (63). The AES evaluates participants’ pretreatment expectations regarding acupuncture intervention, with higher scores indicating greater expectancy. Scores >12 indicate high expectancy, whereas scores ≤12 indicate low expectancy (64). The AES was administered once prior to treatment initiation.

(6) *Blinding assessment*

Blinding effectiveness will be evaluated by asking participants whether they perceived needle penetration during treatment. Assessments will be conducted at three time points: baseline (after the first treatment session), mid-term (end of week 3), and final (end of week 6, after the last treatment session). Participants will also be asked to guess their group assignment (electroacupuncture, sham, or unsure) and to rate their confidence level. The blinding index will be calculated at each time point. If systematic unblinding is detected, sensitivity analyses will be performed excluding participants who correctly guessed their assignment with high confidence.

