### Statistical analysis

All statistical analyses will be conducted using SPSS version 28.0 (IBM Corp., Armonk, NY, United States) according to the intention-to-treat principle. A two-sided *p* < 0.05 will be considered statistically significant.

Continuous variables will be summarized as mean ± standard deviation or median (interquartile range), as appropriate. Categorical variables will be presented as frequencies and percentages. Between-group differences at single time points will be assessed using independent-samples *t*-tests or Mann–Whitney U tests for continuous variables and *χ*^2^ or Fisher’s exact tests for categorical variables.

Longitudinal outcomes will be analyzed using linear mixed-effects models with fixed effects for group, time, and group-by-time interaction, and random intercepts for participants. Missing data will be handled using likelihood-based estimation under the missing-at-random assumption. Multiple imputation will be conducted as a sensitivity analysis.

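### Low attendance withdraws a participant from the study, and the plan does not say that outcome collection continues, which conflicts with the intention-to-treat principle

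*Protocol article*

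**What the plan says.** The Withdrawal criteria section has a single list, opened by "Participants will be withdrawn from the study if any of the following occur". Item 5 of that list is "Poor treatment compliance, defined as attendance at fewer than 50% of scheduled acupuncture sessions". Item 1 is "Participants who develop intolerable severe withdrawal symptoms during the NBZDs tapering process" and item 6 is "Occurrence of adverse events that preclude continued participation or pose a risk to participant safety". The remaining items are the participant's own request (item 2), withdrawal of consent (item 3) and newly arising exclusion criteria (item 4). The article has no second list for stopping trial treatment only, and no sentence on outcome collection after withdrawal. Table 1 records reasons for dropout or withdrawal at every week.

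Under Primary outcome measures, success means having "completely ceased NBZDs use (any dose) during the final week of treatment (days 36–42"). The source is stated there too: "Medication adherence was verified using patients’ daily diaries and medication records". The NBZDs tapering protocol section provides telephone contact twice a week during treatment. Under Secondary outcome measures, "some participants will be followed up online (video/phone) at week 10". The Statistical analysis section promises analysis "according to the intention-to-treat principle". The Data management section makes the same commitment for the full analysis set and handles missing outcomes by likelihood-based mixed models under missing at random, with multiple imputation as a sensitivity analysis.

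**The concern.** Intention-to-treat requires that participants be followed as randomised, whatever their adherence. Item 5 does the reverse, because poor adherence itself ends participation in the study. Attendance is observed after allocation and may depend on it: a participant may stop coming because needling is uncomfortable, or because the taper is going badly and no benefit is felt. In either case, those who leave probably differ in their chance of stopping NBZDs, and the reasons may differ between arms.

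The definition of the full analysis set does not solve this. It keeps a low attender who had one session and one post-baseline assessment, but it cannot supply a week-6 outcome that was not recorded. The loss would also be largely avoidable, since the primary outcome requires no acupuncture session.

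**Working it through.** **When item 5 is met.** Table 1 gives 18 sessions, and the Acupuncture procedure section gives three per week for 6 weeks.
- Half of 18 is 9, so attending 8 or fewer meets the criterion. That is 18 − 8 = 10 missed sessions.
- Earliest: all of sessions 1 to 10 are missed. Weeks 1 to 3 hold 3 × 3 = 9 sessions, so session 10 is the first of week 4 (days 22–28), before the primary window opens on day 36.
- Latest: the tenth missed session is session 18, at the end of week 6, when the primary window is essentially over.

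An early trigger therefore costs the week-6 and week-10 data. A trigger near session 18 costs mainly the follow-up data.

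**What the outcomes need.** Set side by side, the sections show that:
- the primary outcome uses diaries and medication records, with prescription cross-checks;
- contact by telephone already exists in weeks 1 to 6;
- remote assessment is accepted for some participants at week 10;
- week-6 polysomnography needs a visit, and diary cards are normally returned at weekly visits;
- only the final blinding check is tied to the last acupuncture session.

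**The plan's own figures.** The Sample size section states 32 per group, a 20% dropout allowance and 39 per group. The step from 32 to 39 reproduces as 32 × 1.2 = 38.4, rounded up. Dividing by 1 − 0.20 would give 40. This point does not depend on that difference.

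**Possible size.** The number who will meet item 5 is not given. As an assumption, let the whole dropout allowance fall on the week-6 outcome, equally in both arms.
- 0.20 × 39 = 7.8, about 8 per arm, leaving 39 − 8 = 31 observed.
- With s successes among the 31, the rate among all 39 lies between s/39 and (s + 8)/39. The width of this range is 8/39 = 20.5 points.
- With 4 missing instead of 8, the width is 4/39 = 10.3 points.

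**Power.** The assumed rates are p1 = 0.50 and p2 = 0.1083, with two-sided α = 0.05. The difference is 0.3917 and the mean rate 0.30415. Power = Φ{[0.3917√n − 1.96 √(2 × 0.30415 × 0.69585)] / √(0.25 + 0.0966)}.
- n = 39: (2.446 − 1.275)/0.589 = 1.99, power 97.7%.
- n = 31: (2.181 − 1.275)/0.589 = 1.54, power 93.8%.

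Under the plan's own rates, power stays above the 90% target even with 8 lost per arm. What is at stake is bias.

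**The case against.** The article nowhere says that assessment stops on withdrawal. It condenses a fuller protocol, which may provide for continued follow-up. That stands as a reason to word the loss conditionally. It does not remove the point, because the stated rule is withdrawal from the study, ending data collection is its natural reading, and nothing in the article softens it.

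A reader might infer more than the documents support:
- **That every low attender loses the week-6 outcome.** The timing above shows otherwise. For anyone meeting item 5, the week-2 assessment precedes withdrawal, and often the week-4 assessment does too.
- **That item 6 has the same defect in full.** Its wording covers events that preclude continued participation or pose a safety risk, not events that merely preclude acupuncture. Some of these participants may be impossible to follow.
- **That nothing at week 6 needs attendance.** Scales are completed in the treatment room and polysomnography needs a visit. The telephone calls are described only for the treatment period, and remote follow-up only for some participants at week 10.
- **That a spurious effect of a particular size follows.** With a true rate of 30% in both arms, losing 8 failures from one arm only would give 11.7/31 = 37.7%, a gap of about 8 points. That is a constructed extreme. It assigns the whole all-cause allowance to low attendance, assumes that all 8 failed, and uses observed cases only, although the plan has missing-data methods. No figure in the article supports that pattern.
- **That the trial becomes a comparison among compliers.** This is too strong, since the full analysis set does not exclude low attenders.

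**Conclusion.** The point holds for item 5. Withdrawal from the study for low attendance conflicts with the stated intention-to-treat principle, and read as written it can remove primary and week-10 outcomes that are obtainable without any acupuncture session. Missing at random may not repair this, because low attendance is plausibly tied to how the taper is going.

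The size and direction are unknown. The bound of 20.5 points in one arm's rate assumes that all 8 of the planned dropouts per arm lack the week-6 outcome. It is a ceiling under that assumption and not an expected bias. Power is not affected to any important degree. The conclusion rests on reading withdrawal from the study as the end of data collection.

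Item 1 raises a related matter. The Withdrawal criteria remove participants with intolerable severe withdrawal symptoms, while the NBZDs tapering protocol answers intolerable symptoms by a return to the previous dose level and a new attempt. The two passages must be reconciled.

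**What to change.** Limit the change to data collection, and leave the clinical criteria for stopping treatment to the sponsor.
1. Remove attendance below 50% as a reason to leave the study, and report it as adherence.
2. State that, whatever the listed reason for stopping trial treatment (items 1, 2, 4, 5 and 6), the medication diary, prescription check, questionnaires and adverse-event contacts continue to week 10, remotely if needed. The exceptions are a participant who withdraws consent for data collection or who cannot be followed.
3. Under item 2, ask whether the participant is stopping treatment, data collection or both, and record the answer.
4. Reconcile item 1 with the rule for intolerable symptoms in the NBZDs tapering protocol.

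The cost is protocol wording and a few extra telephone or video contacts, by routes the article already uses. Some participants who stop sessions will still decline the assessments, so the loss is reduced and not abolished. No stated sample size changes.

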### Interventions

All acupuncture procedures will be performed by a licensed acupuncturist holding a master’s degree in acupuncture and massage from Zhejiang Chinese Medical University, with more than 8 years of formal training and at least 3 years of independent clinical practice. Prior to trial initiation, all study personnel will undergo standardized training to ensure protocol adherence and procedural consistency.

### Electroacupuncture group

Participants in the electroacupuncture group will receive electroacupuncture treatment in addition to a standardized NBZDs tapering protocol.

### NBZDs tapering protocol

Based on the 2025 European clinical practice guideline recommending a gradual dose reduction of 10–25% per week for NBZDs (27), and supported by two clinical studies that successfully employed a weekly 25% reduction strategy (21, 28), NBZDs will be reduced at a rate of 25% of the baseline dose per week. If participants experience intolerable withdrawal symptoms during tapering—such as exacerbation of insomnia, anxiety, or agitation—the dose will be temporarily reverted to the previous level. Tapering will be reattempted during the subsequent evaluation cycle (1 week per cycle).

Throughout the treatment period, participants will attend weekly in-person consultations and receive twice-weekly telephone follow-ups. Dose adjustments will be conducted through a shared decision-making process, enabling participants to actively engage in symptom monitoring and self-management under physician supervision. Final dosage modifications will require investigator approval.

### Acupuncture procedure

Participants will be treated in the supine position, with bilateral acupoint selection at each session. Acupoints will include Baihui (GV20), Sishencong (EX-HN1), Bilateral Anmian (Extra), Shenting (GV24), Yintang (GV24+), Bilateral Hegu (LI4), Bilateral Taichong (LR3), Bilateral Neiguan (PC6), Bilateral Shenmen (HT7), Bilateral Sanyinjiao (SP6), Bilateral Shenmai (BL62), and Bilateral Zhaohai (KI6) (29, 30).

Acupoints will be localized in accordance with the Nomenclature and Location of Acupoints (GB/T 12346–2021), detailed locations are presented in Table 2 (31). After routine skin disinfection with 75% medical alcohol, sterile disposable acupuncture needles (0.25 × 40 mm; Andy Medical Instruments Co., Ltd., Guizhou, China) will be inserted. Manual manipulation will be applied to elicit the deqi sensation, characterized by soreness, numbness, heaviness, or distension. Electrodes will be connected between Shenting–Baihui, bilateral Sishencong, and Shenmai–Zhaohai using a Yindi KWD-808I electroacupuncture device. A continuous wave at 4 Hz will be applied, with intensity adjusted to participant tolerance. Needles will be retained for 30 min.

**Table 2 tab2:** Acupoint locations.

Acupoint	Location
Baihui (GV20)	5 cun directly above the midpoint of the anterior hairline on the head
Sishencong (EX-HN1)	At the vertex of the head, 1 cun anterior, posterior, and lateral to Baihui (GV20), four points in total
Anmian (Extra)	Posterior to the ear, in the depression between the sternocleidomastoid and trapezius muscles
Shenting (GV24)	0.5 cun directly above the midpoint of the anterior hairline on the head
Yintang (GV24+)	In the depression at the midpoint between the medial ends of the two eyebrows
Hegu (LI4)	On the dorsum of the hand, between the 1st and 2nd metacarpal bones, at the midpoint of the radial side of the second metacarpal bone
Taichong (LR3)	On the dorsum of the foot, in the depression distal to the junction of the first and second metatarsal bones
Neiguan (PC6)	On the palmar aspect of the forearm, 2 cun proximal to the wrist crease, between the tendons of palmaris longus and flexor carpi radialis
Shenmen (HT7)	At the ulnar end of the transverse crease of the wrist, in the depression on the radial side of the tendon of muscle flexor carpi ulnaris
Sanyinjiao (SP6)	On the tibial aspect of the leg, 3 cun proximal to the tip of the medial malleolus, on the posterior border of the tibia
Shenmai (BL62)	On the lateral side of the foot, in the depression directly below the tip of the lateral malleolus
Zhaohai (KI6)	On the medial side of the foot, in the depression on the inferior border of the medial malleolus, vertically below the apex of the medial malleolus

Treatment will be administered three times per week on alternating days for 6 consecutive weeks. Standardized medication tapering interviews will be conducted prior to weekly acupuncture sessions.

### Sham electroacupuncture group

Participants in the sham electroacupuncture group will receive non-penetrating sham acupuncture in combination with the same standardized NBZDs tapering protocol. Participants will be treated in the supine position using the same acupoint locations as in the electroacupuncture group. After skin disinfection, retractable blunt-tip needles (0.25 × 40 mm; Shanghai Hongman Technology Co., Ltd., China) will be placed within a spacer and tapped to simulate needle insertion without skin penetration. This procedure produces a pricking sensation comparable to real acupuncture while avoiding tissue penetration.

Needles will be connected to the same electroacupuncture device; however, no electrical current will be delivered, despite activation of the device indicator light. Needles will remain in place for 30 min without current adjustment. Treatment frequency and duration will be identical to those of the electroacupuncture group.

### Concomitant medication

Throughout the study period, participants will not be permitted to use any additional pharmacological treatments that may affect sleep, mood, or autonomic function, including antidepressants, anxiolytics, antipsychotics, melatonin, and melatonin receptor agonists.

Medications prescribed for stable chronic medical conditions (e.g., hypertension, diabetes, or dyslipidemia) will be allowed, provided that the dosage has remained unchanged for at least 4 weeks prior to enrollment and throughout the study period.

Any temporary or emergency medication use will be documented in detail, including the drug name, dosage, duration, and indication, and will be considered in subsequent analyses if necessary.

### Outcome measures

#### Primary outcome measures

The successful discontinuation rate at the end of the 6-week treatment was defined as the proportion of patients who had completely ceased NBZDs use (any dose) during the final week of treatment (days 36–42). Medication adherence was verified using patients’ daily diaries and medication records. Patients completed a daily diary card, on which they recorded the date, medication name, dose, time of administration, and any adverse reactions. The diary cards were returned to the physician at each weekly visit, and prescription records were cross-checked by an independent observer every 3 weeks. Any discrepancy between the diary and medication records will be resolved by consensus of two blinded independent investigators based on all available data (daily diaries, medication records). Urine or blood drug concentration testing was not performed to confirm participants’ self-report of hypnotic discontinuation, due to the short half-life of NBZDs (requiring daily sampling, which is logistically infeasible) and the increased participant burden that would likely raise dropout rates. The multi-source adjudication approach described above was considered a reliable alternative.

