Various strategies have been explored to facilitate safe and effective BZRAs discontinuation. Pharmacological substitution approaches, although commonly employed, may provoke adverse effects such as panic symptoms (12), increase fall risk (13, 14), or anticholinergic side effects including dry mouth and dysgeusia (15). Moreover, individualized and standardized protocols for BZRAs dose conversion and tapering remain inadequately established (16). In the absence of medications specifically approved by the U.S. Food and Drug Administration or the China National Medical Products Administration for BZRAs dependence or withdrawal, non-pharmacological approaches have attracted increasing attention. Acupuncture has been incorporated into the most recent Chinese clinical guidelines for the diagnosis and treatment of insomnia as a recommended therapeutic option (17, 18). As a widely utilized complementary therapy for insomnia, acupuncture has demonstrated efficacy in improving total sleep time, sleep efficiency, and both subjective and objective sleep quality, while also alleviating cognitive impairment and mood disturbances, with a favorable safety profile (19, 20).

More recently, interest has emerged in the potential role of acupuncture as an adjunctive intervention during BZRAs tapering. A randomized controlled trial by Yeung et al. found no significant difference between electroacupuncture and sham acupuncture in discontinuation rates or withdrawal symptom severity during a four-week tapering protocol (21). Subsequent methodological analyses suggested that the inclusion of both BZDs and NBZDs within the same cohort may have confounded the findings, as different BZRAs subtypes are associated with distinct pharmacokinetic profiles and withdrawal trajectories (22).

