#### Secondary outcome measures

Secondary outcomes are assessed at baseline, during treatment, and during follow-up. Detailed assessment procedures are provided in the Supplementary Appendix S1; assessment time points are summarized in Table 1.

(1) *Subjective Sleep Scales*

① Consensus Sleep Diary (CSD): Records total sleep time (TST), sleep onset latency (SOL), wake after sleep onset (WASO), sleep efficiency (SE), subjective sleep quality, and medication use (32–35).

② Insomnia Severity Index (ISI): 7-item scale (0–28) (36); scores ≥15 indicate clinically significant insomnia (37); a reduction of ≥8 points indicates meaningful improvement (38).

③ Pittsburgh Sleep Quality Index (PSQI): Global sleep quality (0–21); scores > 5 indicate poor sleep quality (39–42).

(2) *Daytime Functioning Assessment*

① Epworth Sleepiness Scale (ESS): Daytime sleepiness across eight situations (43, 44).

② Fatigue Severity Scale (FSS): 9-item scale (9–63); scores ≥36 indicate clinically significant fatigue (45–47).

③ Generalized Anxiety Disorder 7-item Scale (GAD-7): Anxiety severity (0–21) (48–50).

④ Patient Health Questionnaire-9 (PHQ-9): Depression symptom severity (51, 52).

(3) *Medication Reduction Response Assessment*

① NBZDs Reduction Rate

The NBZDs reduction rate was calculated using the following formula: NBZDs reduction rate = (Pre-treatment weekly NBZDs dose - Post-treatment weekly NBZDs dose) / Pre-treatment weekly NBZDs dose * 100% (Note: Pre-treatment refers to the baseline period, and post-treatment refers to week 6 of the treatment period) (16).

② Benzodiazepine Hypnotics Withdrawal Symptom Scale (BHWSS): 12-item self-report (3-point scale) assessing withdrawal symptoms (53, 54).

③ Medication Craving Visual Analogue Scale (VAS): 0–10 scale (0 = no craving, 10 = extreme craving) (55).

(4) *Objective sleep assessment parameters*

① Polysomnography (PSG): performed as the primary objective sleep assessment, with all participants undergoing one night of 8-h monitoring during screening to exclude other sleep disorders; sleep stages and parameters were manually scored according to the AASM Manual (Version 3.0) (56–58).

② Actigraph (ACT): Recorded for 7 consecutive days at baseline and at the end of intervention; parameters included number of awakenings (NOA), total wake time (TWT), sleep onset latency (SOL), total sleep time (TST), and sleep efficiency (SE) (59–62).

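### The primary outcome counts only absence of NBZDs on days 36–42, and no rule says how a participant who takes another sedative or sleep drug is scored

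*Protocol article*

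**What the plan says.** All references are to the protocol article.

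- **Primary outcome measures.** Success is "the proportion of patients who had completely ceased NBZDs use (any dose) during the final week of treatment (days 36–42". On the daily card participants "they recorded the date, medication name, dose, time of administration, and any adverse reactions". Adjudication is limited: "Any discrepancy between the diary and medication records will be resolved by consensus of two blinded independent investigators".
- **Concomitant medication.** During the study "participants will not be permitted to use any additional pharmacological treatments that may affect sleep, mood, or autonomic function". The only sentence on analysis concerns temporary or emergency use, which is documented and "will be considered in subsequent analyses if necessary".
- **Exclusion criteria, item 3.** Anxiolytics, antidepressants, antipsychotics, melatonin and melatonin receptor agonists are excluded, both before screening and during the study.
- **Withdrawal criteria, item 4.** A reason for withdrawal is "Emergence of exclusion criteria during the study period".
- **Data management.** The full analysis set keeps every randomized participant with at least one session and one post-baseline assessment. Missing outcomes are handled by likelihood-based mixed models assuming missing at random, with multiple imputation as a sensitivity analysis.
- **Secondary outcome measures.** For the NBZD reduction rate, "post-treatment refers to week 6 of the treatment period". Table 1 schedules that rate at baseline and at weeks 2, 4, 6, 8 and 10.

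**The concern.** A participant can stop the NBZD and take something else to sleep. The primary definition does not look at that event, and the sections that mention other drugs do not give it a score. Depending on the class of drug, the same behaviour can end as a success or as a missing value. Nowhere is it stated to be a failure.

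Both outcomes matter. Counting the event as success misclassifies the primary endpoint. Treating it as missing at random is hard to defend, because someone withdrawn for starting a replacement drug during a taper is plausibly missing because the taper failed. If switching is commoner under sham, a real effect is diluted. If it is commoner under electroacupuncture, the apparent effect is inflated. Leaving the matter to be considered later, if necessary, puts a primary-outcome classification in the hands of a decision that could be taken after the data are seen.

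**Working it through.** **Step 1. Follow an NBZD-free participant who takes another drug on days 36–42.**

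| Drug taken | What the article requires | Primary score |
|---|---|---|
| Class listed in exclusion 3 | Prohibited; withdrawal under item 4 | Not stated: undefined, or missing at random |
| Other sedative or sleep drug (e.g. sedating antihistamine) | Prohibited; no consequence stated | Meets the success definition as worded |
| Temporary or emergency use | Documented; considered if necessary | Not stated |

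Adjudication does not catch the second row. A participant who honestly records the other drug creates no discrepancy between diary and records, so nothing is referred.

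**Step 2. Reproduce the planned sample size.** Inputs from Sample size: P1 = 0.50, P2 = 0.1083, two-sided α = 0.05, power 0.90.

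- Mean rate = (0.50 + 0.1083)/2 = 0.30415; difference = 0.3917.
- Two-proportion formula: [1.96·√(2 × 0.30415 × 0.69585) + 1.282·√(0.25 + 0.09657)]² / 0.3917² = (1.275 + 0.755)² / 0.1534 = 26.9, so 27.
- With continuity correction: (26.86/4) × [1 + √(1 + 4/(26.86 × 0.3917))]² = 31.8, so 32 per group. This matches the stated 32.
- The arcsine formula named in the article gives 1641.4 × (3.242/25.79)² = 25.9, so 26. That mismatch is a separate matter, and the present point does not rest on it.
- After 20% dropout from 39: 39 × 0.8 = 31.2, so about 31 evaluable per arm.

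**Step 3. Effect of switchers counted as successes.** The article gives no switching rate, so the rates below are assumptions. Each switcher is taken to be a failure otherwise. Power is exact binomial at 31 per arm, summing the probabilities of all outcome pairs with a two-sided p < 0.05.

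| Assumption | EA vs sham as scored | Fisher | χ² |
|---|---|---|---|
| No switching | 50% vs 10.83% | 0.908 | 0.945 |
| 10% of each arm | 60% vs 20.83% | 0.852 | 0.905 |
| 10% of the failures in each arm | 55% vs 19.7% | 0.769 | 0.840 |
| 5% of sham only | 50% vs 15.83% | 0.770 | 0.840 |
| 10% of sham only | 50% vs 20.83% | 0.589 | 0.686 |

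Ten per cent of the sham arm is about 4 of 39, roughly as many as the planned sham successes (0.1083 × 39 = 4.2). In the opposite direction, 10% switching under electroacupuncture alone would raise the apparent difference from 39.2 to 60 − 10.83 = 49.2 percentage points.

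**Step 4. Effect of the fix if the planning rates already contain switchers.** Suppose an equal share of apparent successes in each arm is rescored as failure. With the normal approximation (pooled variance, no continuity correction) at 32 per group:

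| Share rescored | Rates | Power |
|---|---|---|
| 0% | 50% vs 10.8% | 94% |
| 10% | 45% vs 9.7% | 91% |
| 20% | 40% vs 8.7% | 85% |
| 30% | 35% vs 7.6% | 78% |

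**Step 5. Reduction rate.** The formula takes the post-treatment dose at week 6 only. Table 1 asks for the rate at weeks 2, 4, 6, 8 and 10. As written, the formula cannot produce the values at weeks 2, 4, 8 and 10.

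**The case against.** A reader might infer that anyone who switches drugs counts as a success. The article does not support that. Added drugs that may affect sleep or mood are prohibited, and the classes in exclusion 3 lead to withdrawal. For those classes the score is undefined. A benzodiazepine could plausibly be read as an anxiolytic and so fall there. The literal success reading applies to barred drugs outside the listed classes.

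A reader might also take the Introduction's "Pharmacological substitution approaches, although commonly employed" as evidence that switching will be frequent. That sentence describes strategies for helping people stop these drugs. It says nothing about participants changing drugs in a trial that forbids it and has weekly visits, twice-weekly calls, a diary with drug names and prescription checks. Those safeguards should keep switching uncommon, but they do not say how it is scored when it happens.

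The 59% figure is a one-sided case. It needs switching in sham only, with every switcher otherwise a failure and none withdrawn. Equal switching costs much less. The 10.83% comes from a cited trial whose endpoint definition is not visible here, so it may or may not already include switchers.

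Two further objections have some force. The endpoint matches the stated objective of reducing NBZD use, so widening it is partly a choice of estimand, and a strict rule would fail someone for a single documented emergency dose. Keeping the NBZD-only definition as a sensitivity analysis answers both. Scoring of prohibited medication is also often left to an analysis plan, which is not shown. Here, however, the primary definition is itself stated, and it is fixed on NBZDs alone. A later rule would have to override it.

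**Conclusion.** The concern holds in this form: the primary definition ignores every drug except NBZDs, and no section scores use of another sedative or sleep drug as failure. Such use leads either to an undefined or missing-at-random outcome (listed classes) or to a literal success (other barred drugs). It should be corrected in the endpoint wording.

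Its size cannot be fixed from the article. Under the assumptions shown, Fisher power at 31 per arm moves from 91% to 85% with 10% switching in each arm, and to 59% with 10% in sham only. These are illustrations and not predictions. They assume that the planned rates of 50% and 10.83% exclude switchers.

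The conflict between the reduction-rate formula and Table 1 is real but separate, and it concerns a secondary outcome only.

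**What to change.** 1. In the primary definition, state that a participant who takes any other prohibited hypnotic, sedative, anxiolytic or sleep-promoting drug on days 36–42, or who is withdrawn for such use, is scored as not discontinued.
2. Identify such use from the medication names on the diary card and from the prescription records, and have the two blinded investigators review it as well as the discrepancies they already resolve.
3. In Concomitant medication, replace the open-ended sentence on later consideration with a reference to this rule, so that temporary or emergency use is covered explicitly.
4. Report the NBZD-only definition as a sensitivity analysis.
5. Reconcile the time point in the reduction-rate formula with the visits in Table 1.

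The cost is wording and a modest extension of adjudication. No new data are needed, and no dose, taper or rescue rule changes. The downside is that success rates may be slightly lower, with the loss of power shown in step 4 if the planning rates already include switchers.
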